## **Exploratory Outcome measures**

### **Parkinson's Disease Questionnaire-39 (PDQ-39)**

A hard copy of PDQ-39 questionnaire was provided at each time point to assess the perceived difficulties in daily life as a result of having Parkinson's disease. The sum of scores from 39 questions gave the PDQ-39 score (range 0-156). The higher the score, the larger the perceived difficulties in daily life.

*Outcome measure:* PDQ-39 total score

### **Beck Depression Inventory (BDI-II)**

A hard copy of BDI-II questionnaire was provided at each time point to assess the participants' feelings/ and emotions. Data were manually entered into the computer by the examiner to derive the score. The sum of the scores from all 21 questions gave the BDI-II total score (range 0-63). The higher the score, the greater the magnitude of depression. Participants with a total score of  $\leq 13$  are classified of having minimal depression, between 14-19 mild, between 20-28 moderate and  $\geq 29$  severe depression.

*Outcome measure:* BDI-II total score

### **2. Movement Disorder Society-Unified Parkinson's Disease Rating Scale (MDS-UPDRS)**

A hard copy of the UPDRS Patient Questionnaire (Part I- Non-motor Aspects and Part II- Motor Aspects of Experiences of Daily Living) was provided to the participant at each time point. Sections of the questionnaire on cognitive aspects (Part I), motor examination (Part III) and motor complications (Part IV) were administered by the same examiners at each time point. The sum of the scores from all four parts of the questionnaire gave the MDS-UPDRS Total score (range 0-260).

The Hoehn and Yahr score indicated the severity of Parkinson's disease (range 0-5) at baseline. The sum of the scores from Part III gave the UPDRS Motor score (range 0-132). The higher the scores, the worse the Parkinson's Disease-related disability and impairment.

**Outcome measure:** MDS-UPDRS Total score, MDS-UPDRS Motor score

**Figure S1. Weekly actigraphy light exposure (lux) data**

Group means (95% CIs) for daytime light exposure across the 6-week study duration. Error bars represent 95% CIs. Day Mel=Daylight Melanopsin group (blue circles with blue error bars). Enhanced Mel=Enhanced Melanopsin group (purple triangles with purple error bars).

[figure not shown]

**Figure S2. Melanopsin function (6s PIPR) at baseline, week 4 and week 6**

**A.** The mean post-illumination pupil light response (PIPR %) (95% CIs) as a measure of melanopsin function in both groups randomised to either Daylight Melanopsin (Day Mel:  $n = 27$ , blue columns with blue error bars) or Enhanced Melanopsin (Enhanced Mel:  $n = 28$ , purple columns with purple error bars) compared to an age-matched, healthy control group ( $n = 10$ , black columns with black error bars) at baseline (healthy control data from the Medical Retinal laboratory, QUT). Error bars represent 95% CIs. The higher the PIPR %, the better the melanopsin function. Melanopsin function is significantly reduced in both light intervention groups compared to a healthy age-matched control group ( $p < 0.01$ ). **B.** The PIPR (with 95% CIs) in both groups) at week 4 (Day Mel:  $n = 25$ , Enhanced Mel:  $n = 25$ ) and **C.** at week 6 (Day Mel:  $n = 27$ , Enhanced Mel:  $n = 25$ ), with an increase in melanopsin function in the Enhanced Mel group.

| Time point                                                                                                                                                                                                                                                                                                                                                                    | Day Mel                    | Enhanced Mel               | Mean Difference-Group   | p value Group | Time point | Mean Difference-Time     | p value Time | p value Group x Time |
|-------------------------------------------------------------------------------------------------------------------------------------------------------------------------------------------------------------------------------------------------------------------------------------------------------------------------------------------------------------------------------|----------------------------|----------------------------|-------------------------|---------------|------------|--------------------------|--------------|----------------------|
| Exploratory Outcomes                                                                                                                                                                                                                                                                                                                                                          |                            |                            |                         |               |            |                          |              |                      |
| PDQ-39 total score                                                                                                                                                                                                                                                                                                                                                            |                            |                            |                         |               |            |                          |              |                      |
| BL                                                                                                                                                                                                                                                                                                                                                                            | 37.61 (30.93 to 44.28); 27 | 30.29 (23.96 to 36.62); 30 | -7.31 (-16.40 to 1.78)  | 0.12          | WK4-BL     | -5.38 (-7.95 to -2.81)   | <0.0001      | 0.05                 |
| Wk4                                                                                                                                                                                                                                                                                                                                                                           | 29.46 22.79 to 36.13); 27  | 27.69 (21.25 to 34.13); 26 | -1.77 (-10.93 to 7.39)  | 0.71          | WK6-BL     | -6.81 (-9.38 to -4.24)   | <0.0001      |                      |
| Wk6                                                                                                                                                                                                                                                                                                                                                                           | 27.87 (21.19 to 34.54); 27 | 26.42 (19.98 to 32.86); 26 | -1.44 (-10.60 to 7.72)  | 0.76          | WK6-WK4    | -1.43 (-4.01 to 1.15)    | 0.53         |                      |
| BDI-II total score                                                                                                                                                                                                                                                                                                                                                            |                            |                            |                         |               |            |                          |              |                      |
| BL                                                                                                                                                                                                                                                                                                                                                                            | 11.60 (8.97 to 14.23); 27  | 10.20 (7.71 to 12.70); 30  | -1.40 (-4.99 to 2.19)   | 0.45          | WK4-BL     | -1.50 (-2.81 to -0.19)   | 0.07         | 0.23                 |
| Wk4                                                                                                                                                                                                                                                                                                                                                                           | 9.08 (6.45 to 11.71); 27   | 9.72 (7.16 to 12.29); 26   | 0.64 (-2.99 to 4.28)    | 0.73          | WK6-BL     | - 1.84 (-3.15 to -0.53)  | 0.02         |                      |
| Wk6                                                                                                                                                                                                                                                                                                                                                                           | 9.71 (7.08 to 12.34); 27   | 8.42 (5.85 to 10.98); 26   | -1.30 (-4.93 to 2.34)   | 0.49          | WK6-WK4    | -0.34 (-1.65 to 0.97)    | 0.87         |                      |
| MDS-UPDRS- Total score                                                                                                                                                                                                                                                                                                                                                        |                            |                            |                         |               |            |                          |              |                      |
| BL                                                                                                                                                                                                                                                                                                                                                                            | 50.60 (43.53 to 57.66); 27 | 44.26 (37.56 to 50.97); 30 | -6.33 (-15.96 to 3.29)  | 0.20          | WK4-BL     | -5.81 (-9.40 to -2.22)   | 0.01         | 0.76                 |
| Wk4                                                                                                                                                                                                                                                                                                                                                                           | 44.39 (37.18 to 51.59); 24 | 38.85 (31.37 to 46.34); 17 | -5.53 (-15.87 to 4.80)  | 0.30          | WK6-BL     | - 6.51 (-10.06 to -2.96) | 0.002        |                      |
| Wk6                                                                                                                                                                                                                                                                                                                                                                           | 45.01 (37.80 to 52.22); 24 | 36.82 (29.41 to 44.23); 18 | -8.19 (-18.46 to 2.08)  | 0.12          | WK6-WK4    | -0.70 (-4.33 to 2.93)    | 0.92         |                      |
| MDS-UPDRS- Motor score                                                                                                                                                                                                                                                                                                                                                        |                            |                            |                         |               |            |                          |              |                      |
| BL                                                                                                                                                                                                                                                                                                                                                                            | 21.01 (16.61 to 25.41); 27 | 16.47 (12.29 to 20.65); 30 | -4.54 (-10.53 to 1.46)  | 0.14          | WK4-BL     | -1.86 (-4.15 to 0.43)    | 0.26         | 0.72                 |
| Wk4                                                                                                                                                                                                                                                                                                                                                                           | 19.53 (15.03 to 24.03); 24 | 14.22 (9.53 to 18.92); 17  | -5.31 (-11.77 to 1.16)  | 0.11          | WK6-BL     | -2.09 (-4.36 to 0.18)    | 0.18         |                      |
| Wk6                                                                                                                                                                                                                                                                                                                                                                           | 19.86 (15.37 to 24.36); 24 | 13.44 (8.80 to 18.08); 18  | -6.43 (-12.85 to -0.01) | 0.05          | WK6-WK4    | -0.23 (-2.56 to 2.10)    | 0.98         |                      |
| Data are average means (95% CIs) and the number of participants for all the exploratory outcome measures. BL= Baseline. Wk4=Week 4. Wk6=Week6. Day Mel=Daylight Melanopsin group. Enhanced Mel=Enhanced Melanopsin group. PDQ=Parkinson’s Disease Questionnaire. BDI=Beck Depression Inventory. MDS-UPDRS=Movement Disorder Society-Unified Parkinson’s Disease Rating Scale. |                            |                            |                         |               |            |                          |              |                      |
| Table S1: Exploratory outcomes, estimated by mixed models                                                                                                                                                                                                                                                                                                                     |                            |                            |                         |               |            |                          |              |                      |

| Group                                                                                                                                                                                                                                                          | Time of light therapy: Mean (SD) |             |             |             |               |
|----------------------------------------------------------------------------------------------------------------------------------------------------------------------------------------------------------------------------------------------------------------|----------------------------------|-------------|-------------|-------------|---------------|
|                                                                                                                                                                                                                                                                | Wk1                              | Wk2         | Wk3         | Wk4         | Average 4 wks |
| Day Mel                                                                                                                                                                                                                                                        | 7:22 (1:39)                      | 7:30 (1:47) | 7:31 (1:50) | 7:23 (1:32) | 7:26 (1:37)   |
| Enhanced Mel                                                                                                                                                                                                                                                   | 6:56 (1:39)                      | 7:02 (1:42) | 6:54 (1:29) | 7:07 (1:31) | 6:56 (1:33)   |
| Data are average means (SDs) of the timing of light therapy for each group. Wk1=Week1. Wk2= Week2. Wk3=Week3. Wk4=Week4. Average 4 wks= Average of all four weeks of light therapy. Day Mel=Daylight Melanopsin group. Enhanced Mel=Enhanced Melanopsin group. |                                  |             |             |             |               |
| Table S2: Timing of light, averaged each week and total average per group                                                                                                                                                                               |                                  |             |             |             |               |

[figure not shown][figure not shown][figure not shown]

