## Supplementary Methods

### Statistical analyses

#### Outcome measures

The plan for analysis of the data was decided upon before the commencement of the analyses and was formulated by the Researchers based on scientific rather than statistical grounds. Furthermore, and given the longitudinal nature of the data it was decided to fit a mixed model in each case, with a random intercept for each participant. Time in all cases was fitted as a categorical fixed effect.

Time and group were fitted as fixed effects along with their interaction. Participant ID was fitted as random effect with the inclusion of age, disease stage, disease duration and LEDD (Levodopa dosage).

The model was fitted for all outcome variables. Following the analyses, the resultant models objects were processed in order to derive appropriate estimated marginal means. All mixed model analyses was performed in R using “lmerTest”, “tidyverse”, “flextable”, “openxlsx”, “janitor”, and “emmeans”, and custom written codes in R.

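### In Table S1 the time-contrast p values and 95% CIs appear to come from different methods, and in one row (BDI-II, week 4 minus baseline) they disagree at the 5% level

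*Combined protocol and SAP*

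**What the plan says.** Table S1 gives, for each of four exploratory outcomes, three pairwise time contrasts (week 4 minus baseline, week 6 minus baseline, week 6 minus week 4), each with an interval and a p value. The footnote calls the intervals 95% CIs and says nothing about adjustment. All quoted estimates are negative; the quoted runs leave out the leading minus sign and the closing bracket.

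- BDI-II, week 4 minus baseline: "1.50 (-2.81 to -0.19", p = 0.07.
- BDI-II, week 6 minus baseline: "1.84 (-3.15 to -0.53", p = 0.02.
- BDI-II, week 6 minus week 4: "0.34 (-1.65 to 0.97", p = 0.87.
- PDQ-39, week 4 minus baseline: "5.38 (-7.95 to -2.81", p < 0.0001.

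On method, the Supplementary Methods (Statistical analyses, Outcome measures) say only that the fitted models were "processed in order to derive appropriate estimated marginal means". Section 6.2 of the protocol adds that the mixed models are used for post hoc comparisons by group and time point. Neither place names a p-value adjustment or an interval method for these contrasts. The only correction named anywhere is Bonferroni, for the baseline pupil comparison.

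**The concern.** A two-sided p value and a 95% CI from the same procedure must agree on whether zero is excluded. In the BDI-II week 4 row they do not, so a reader who looks at the interval sees a fall in depression score that passes the 5% level, and a reader who looks at the p value does not. If the two columns follow different rules, the mismatch also runs through the other time-contrast rows even where it changes no conclusion: the intervals are then too narrow for the error rate that the p values use, and nothing in the table says so.

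**Working it through.** **Inputs.** Estimates, limits, p values and counts are from Table S1. There are three time points (section 6.2), hence three pairwise time contrasts per outcome. Degrees of freedom are not printed and are assumed. Observations less participants give 163 - 57 = 106 for PDQ-39 and BDI-II and 140 - 57 = 83 for MDS-UPDRS; allowing for fixed effects, about 104 and 82 were used. Values down to 60 give the same conclusion.

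**Formulae.** SE = half-width / 1.96; t = |estimate| / SE; unadjusted p from the t distribution; Tukey p from the studentized range for three means, evaluated at t × √2.

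**The BDI-II week 4 row.** Half-width = (2.81 - 0.19) / 2 = 1.31. SE = 1.31 / 1.96 = 0.668. t = 1.50 / 0.668 = 2.24. Unadjusted p = 0.027; Tukey p = 0.069, which reproduces the printed 0.07. Rounding does not close the gap: with the least favourable rounding and only 50 df, the unadjusted p is still 0.030. For any df from 50 to 1000 the Tukey p stays between 0.064 and 0.074.

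**All 12 time contrasts.**

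| Contrast | Estimate (half-width) | Unadjusted p | Tukey p | Printed p |
|---|---|---|---|---|
| PDQ-39 WK4-BL | -5.38 (2.57) | 0.00008 | 0.0002 | <0.0001 |
| PDQ-39 WK6-BL | -6.81 (2.57) | <0.0001 | <0.0001 | <0.0001 |
| PDQ-39 WK6-WK4 | -1.43 (2.58) | 0.28 | 0.525 | 0.53 |
| BDI-II WK4-BL | -1.50 (1.31) | 0.027 | 0.069 | 0.07 |
| BDI-II WK6-BL | -1.84 (1.31) | 0.007 | 0.019 | 0.02 |
| BDI-II WK6-WK4 | -0.34 (1.31) | 0.61 | 0.867 | 0.87 |
| UPDRS total WK4-BL | -5.81 (3.59) | 0.002 | 0.006 | 0.01 |
| UPDRS total WK6-BL | -6.51 (3.55) | 0.0006 | 0.0016 | 0.002 |
| UPDRS total WK6-WK4 | -0.70 (3.63) | 0.71 | 0.924 | 0.92 |
| UPDRS motor WK4-BL | -1.86 (2.29) | 0.12 | 0.255 | 0.26 |
| UPDRS motor WK6-BL | -2.09 (2.27) | 0.075 | 0.174 | 0.18 |
| UPDRS motor WK6-WK4 | -0.23 (2.33) | 0.85 | 0.980 | 0.98 |

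Allowing for rounding of the printed estimates and limits, Tukey p values with 1.96 × SE intervals match 11 of 12. The motor WK6-BL row is one that needs that allowance. The alternatives fit much less well: unadjusted p matches at most 2; Bonferroni or Sidak for three contrasts, with 1.96 or t-based intervals, 4 to 5; Tukey p with t-based intervals 7 to 8; Tukey p with Tukey intervals 2. The one miss is PDQ-39 WK4-BL, whose printed p is met by the unadjusted value but not by the Tukey one.

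**Intervals on the Tukey scale.** The Tukey multiplier for three means is about 2.38, and 2.38 / 1.96 = 1.21, so intervals widen by about 21%.

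- BDI-II WK4-BL: -1.50 ± 2.38 × 0.668 = -3.09 to 0.09, which includes zero.
- BDI-II WK6-BL: -3.43 to -0.25.
- PDQ-39 WK4-BL: -8.50 to -2.26.
- UPDRS total WK4-BL: about -10.2 to -1.4.

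Only the first of these changes its reading. In the whole column it is the only row whose 5% conclusion depends on which rule is used.

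**The case against.** The strongest reply is that this is a small reporting inconsistency in a table of exploratory outcomes, that these contrasts pool both arms over time and do not estimate the treatment effect, and that Tukey and 1.96 × SE are nowhere stated. All of that stands and limits the point. It does not remove it: the BDI-II row is inconsistent as printed, whatever the method, and the documents offer no statement that would explain it.

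Three stronger readings are tempting and are not supported.

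- A reader might infer that p values and intervals contradict each other throughout the column. They differ in scale, but they disagree about 5% significance in one row of 12.
- A reader might infer that adjustment was spent on the time effect and withheld from the randomised comparison. The group p values do reproduce as unadjusted, but each time point has a single two-group contrast, so a Tukey adjustment within it changes nothing. Family size explains the difference. Whether to adjust across time points or exploratory outcomes is a separate and debatable question. Nor is the week 6 motor group contrast, "6.43 (-12.85 to -0.01" with p = 0.05, a second contradiction: it implies p = 0.0496 on the normal scale and about 0.054 on a t scale with an assumed 60 df, and both round to 0.05.
- A reader might infer that the primary outcome tables share the problem. The Supplementary Methods say one model was fitted for all outcomes, but not how intervals or p values were made for any table, and no primary or key secondary results table is in these documents.

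**Conclusion.** The point holds in limited form. The time-contrast p values in Table S1 appear to be Tukey-adjusted and the intervals beside them appear to be unadjusted, with no disclosure of either. The consequence at the 5% level is confined to BDI-II week 4 minus baseline. In the other rows the effect is one of precision only. PDQ-39 week 4 minus baseline is a separate anomaly, since its printed p value departs from the rule that the other 11 follow; its conclusion is unaffected. The identification of the methods rests on the numerical fit and on the assumed degrees of freedom, and not on any statement in the plan. The inconsistency in the BDI-II row needs neither assumption to be seen.

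**What to change.** Take the p value and the interval for each contrast from the same method, either Tukey for both or unadjusted for both, using t degrees of freedom. Name that method in the analysis plan and in the Table S1 footnote, then rerun Table S1. Recheck the PDQ-39 week 4 minus baseline p value in the same run. Check whether the other outcome tables, which are not in these documents, were produced in the same way.

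The cost is a rerun of the existing R analysis and a sentence in each place. If Tukey is used for both, the time-contrast intervals widen by about 21% and the BDI-II week 4 interval includes zero. If neither is adjusted, that row's p value becomes about 0.027 and the table should say that no correction was made for three contrasts. As the results are already known, the reason for the choice should be recorded and should not rest on this row.
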